### Analysis for secondary endpoints

#### Secondary outcomes

Secondary outcomes one, two and three will be analysed using relative risk regression, like the primary outcome, with minimally informative priors for all parameters. We will report the probability that EpiDex is superior to placebo, the mean absolute risk difference and relative risk and 95% credible intervals. For secondary outcome four, costs related to health care expenditure, we will undertake a separate formal economic analysis.

#### Safety outcomes

Safety outcomes one, two and three will be analysed using relative risk regression with minimally informative priors [26]. We will report the mean absolute difference, the 95% credible interval and the probability of increased chance of adverse events for EpiDex. The number and percentage of observed events for each of the four safety outcomes will also be reported. Adverse events will be coded using Medical Dictionary for Regulatory Activities (MedDRA) [27] and counted at most once for each participant. We will also present the severity and frequency of the adverse event by System Organ Class.

#### Exploratory outcomes

Exploratory outcomes (a)–(d) will be analysed using relative risk regression and report the posterior mean absolute-risk difference and relative risk with corresponding 95% credible intervals. Exploratory outcomes (e) and (f) are uncensored time-to-event outcomes and will be analysed as a Bayesian Cox proportional hazards model fit with the Integrated Nested Laplace Approximation [28] method in R [29], adjusted for site. We will report median hazard ratios and their corresponding 95% credible intervals.

Exploratory outcome (g) is a repeatedly measured binary outcome and will be analysed using a hierarchical Bayesian relative risk regression to adjust for patients. From this model, we will report mean relative risks alongside 95% credible intervals. Exploratory outcome (h) will initially be analysed using a Bayesian linear model to report the mean difference in expenses alongside a 95% credible interval. Graphical methods will be used to assess normality of residuals, and a lognormal or gamma model will be fit, if required. Exploratory outcomes (i) and (j) will not be analysed at the primary trial analysis of the trial. Thus, a separate analysis plan will be developed before the completion of the 18-year follow-up period.

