#### Exploratory outcomes

The BIPED study will collect 10 additional exploratory outcomes:Admission to hospital for bronchiolitis within 21 days following enrollment ED visit.Intensive care unit (ICU) admissions within 21 days following enrollment ED visit for bronchiolitis and requiring intubation or continuous positive airway pressure (CPAP).All cause hospital admission within 7 days following enrollment ED visit.All cause ED visits within 21 days of enrollment ED visit.Length of stay (in hours) for the enrollment ED visit for participants who are discharged at the enrollment ED visit.Length of hospital admission (in hours) for participants admitted at their enrollment visit.Resolution of symptoms as documented on a standardised questionnaire during the telephone or email at day 7 and 21 days.Out of pocket expenses borne by the family/caregiver in the 21 days following enrollment ED visit.Health care utilisation for respiratory illness up to 18 years of ageDevelopment of respiratory illnesses such as asthma and recurrent wheezing up to 18 years of age.

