## Statistical analysis plan

### Statistical principals

Outcomes will be collected with a standardised survey issued to parents/caregivers either over email or by telephone 7 and 21 days after enrollment in the BIPED study. Non-responders will be sent a second email and, if necessary, up to six attempted phone calls over 3 days. Once 21 days have elapsed following enrolment, the participant’s medical record will be reviewed to track any return ED visits, hospital admissions and additional healthcare contact. Admissions and ED visits reported by caregivers to study hospitals must be confirmed on medical record review. Similarly, at the six study hospitals where admissions and ED visits to non-study hospitals can be confirmed by administrative database review, non-study hospital ED visits and admissions reported on the survey will be confirmed. For study sites where visits and admissions to non-study hospitals cannot be confirmed by administrative database review, the caregiver’s report of and reason for these visits/admissions will be used to determine whether the participant met the study definition of admission. The final trial analysis will take place after every participant has reached 21 days after enrolment and all the data have been collected and cleaned. The analysis will be performed in a blinded manner.

The final trial analysis will use a Bayesian inferential framework based on the posterior probability that the EpiDex combination is superior to placebo for the primary and secondary outcomes. It will follow the intention-to-treat principle. The EpiDex combination will be declared superior to placebo if the posterior probability of superiority is above 99%, with simulations confirming a type 1 error rate of 4.1% with a probability of hospitalisation equal to 0.35 and a power of 81% with a target difference of 8%. Due to the likelihood principle, corrections for multiple comparisons will not be used. All estimates for the treatment effect will be reported using 95% high density posterior credible intervals, calculated using R [18] interfacing with Bayesian software such as JAGS, stan or INLA [19–21].

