### Analysis for the primary endpoint

We will compute the posterior probability that EpiDex results in a lower probability of hospitalisation than placebo using hierarchical Bayesian relative risk regression, adjusted for site. The prior for the treatment effect is from our expert elicitation exercise [17]. We will report the mean and 95% high-density posterior credible interval for the absolute risk difference and relative risk across the two treatment groups. A secondary analysis of the primary outcome will include only those participants who present with their first episode of bronchiolitis. All models will include minimally informative priors for the variance parameters [24] and other coefficients [25].

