### Heterogeneity of treatment effects analysis

Due to the heterogeneity of bronchiolitis, we will also perform a heterogeneity of treatment effect analysis using a predictive approach [30, 31]. We will use a risk modelling approach by developing a multivariable risk model adjusted for, at a minimum, age, sex, prematurity, length of illness at time of enrolment, history of previous wheezing, personal history of eczema, family history of atopy, household smoke exposure, prenatal smoke exposure, breastfeeding and virus type [32, 33] but ignoring treatment assignment. We will create ten risk strata based on this model and report the median treatment effect with 95% credible intervals within each strata using Bayesian risk regression.

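### The posterior mean relative risk with a high-density interval depends on which arm is the numerator; if the ICU outcome is sparse, equal arms would be reported as a relative risk above 1 (minor)

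*SAP article*

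**What the plan says.** The part of the SAP that analyses exploratory outcomes (a) to (d) will "report the posterior mean absolute-risk difference and relative risk with corresponding 95% credible intervals". For outcome (g) it adds that "we will report mean relative risks alongside 95% credible intervals". The primary analysis uses the same pair of summaries: "We will report the mean and 95% high-density posterior credible interval for the absolute risk difference and relative risk across the two treatment groups". Secondary outcomes one to three also get a mean absolute risk difference and a relative risk.

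The interval type is set once, in Statistical principals: "All estimates for the treatment effect will be reported using 95% high density posterior credible intervals".

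One other ratio measure is treated differently. For the length-of-stay outcomes (e) and (f) the plan states: "We will report median hazard ratios and their corresponding 95% credible intervals". The risk-strata analysis will "report the median treatment effect with 95% credible intervals within each strata", without naming the scale of that effect.

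Exploratory outcome (b) is ICU admission for bronchiolitis within 21 days with intubation or CPAP. No expected rate is given for it.

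**The concern.** A relative risk is bounded below by 0 and unbounded above, so its posterior is right-skewed and its mean exceeds its median. The mean is also not reversible: mean(RR) × mean(1/RR) is greater than 1, so with equal arms the relative risk comes out above 1 whether EpiDex or placebo is the numerator. A high-density interval formed on the relative-risk scale is the shortest 95% interval on that scale, so it moves toward zero.

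With many events neither effect can be seen. With few, the point estimate leans toward harm and the interval toward benefit, and both leans would change sides if the ratio were inverted. Outcome (b) is the most severe illness outcome among those reported as a relative risk. A figure clearly above 1 from equal counts could be quoted as a harm signal that the data do not contain.

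**Working it through.** **Inputs.** 410 evaluable infants per arm (Sample size calculation). This ties to the plan's own total: 410 / 0.95 = 431.6, so 432 per arm and 864 in all, as stated. Event counts for (b) are assumed, because the plan gives none. The priors are described only as minimally informative, so several vague forms were tried.

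**Mean relative risk with equal arms.** With x events in each arm and a Jeffreys Beta(0.5, 0.5) prior on each risk, the posterior mean has a closed form:

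E[RR] = E[p1] × E[1/p0] = (x + 0.5)/(x − 0.5) × 410/411

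At x = 4: (4.5/3.5) × (410/411) = 1.28. By symmetry the mean of the inverse ratio is also 1.28. The lognormal approximation exp(1/x − 1/410) gives exp(0.2476) = 1.28.

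| Events per arm | Share of 410 | Mean RR | Median RR |
|---|---|---|---|
| 2 | 0.49% | 1.66 | 1.00 |
| 3 | 0.73% | 1.40 | 1.00 |
| 4 | 0.98% | 1.28 | 1.00 |
| 8 | 1.95% | 1.13 | 1.00 |
| 10 | 2.44% | 1.10 | 1.00 |
| 20 | 4.88% | 1.05 | 1.00 |
| 143 | 34.9% | 1.005 | 1.00 |

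**Sensitivity to the prior at 4 v 4.** Uniform prior on each risk: 1.25. Log-link model with a normal prior on log RR: 1.18 at SD 1, 1.28 at SD 2.5, 1.31 at SD 10. The median stays between 0.96 and 1.00 for every count of two or more and every prior tried.

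**Interval at 4 v 4, Jeffreys prior.**
- High-density on the RR scale: 0.10 to 3.19.
- High-density for placebo over EpiDex: the same numbers by symmetry, which invert to about 0.31 to 9.6 for EpiDex over placebo.
- Equal-tailed: 0.25 to 4.00, and unchanged by inversion.

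Simulation moves the second decimal of these limits slightly.

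**Primary outcome.** Take the planning rate of 35% and the target difference of 8 points: 143 v 111 events in 410 each. The mean RR is (111.5/142.5) × (410/411) = 0.781 and the median 0.777 (Jeffreys prior, ignoring site and the elicited prior). The difference is negligible.

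**The case against.** The strongest reply concerns materiality. The posterior mean with a high-density interval is a recognised, prespecified Bayesian summary, not an error. Superiority is declared on a posterior probability, and subgroup effects on the probability of the interaction, so neither summary decides anything. At 4 v 4 the probability that the relative risk exceeds 1 is one half whatever is printed, both intervals say that almost nothing is known, and the absolute risk difference reported alongside is zero. All of this stands, and it is why the point is minor. It does not remove it: the analysis text for (a) to (d) lists no posterior probability, so for (b) the reader has only the relative risk and the risk difference.

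A reader might infer more than the documents support:

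- That equal arms will be reported as about 30% more risk. That figure needs about 4 events per arm and a vague prior, and the plan states no rate. At 10 v 10 the excess is 10%, at 20 v 20 it is 5%.
- That rare outcomes in general are affected. The safety outcomes are analysed by relative risk regression, but the listed summaries are the mean absolute difference, its interval, the probability of increased harm and the counts, with no relative risk. None of the other outcomes reported as a relative risk is shown to be sparse.
- That the primary result is distorted. It is not, as the 0.781 against 0.777 shows.

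Two textual cautions also stand. For (a) to (d) the word mean could be read as attaching only to the risk difference, although the primary analysis and outcome (g) plainly report a mean relative risk and the natural reading is the same here. And the median in the risk-strata analysis names no scale, so the clear internal precedent is the hazard ratio alone.

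**Conclusion.** The point holds as a minor one. As written, the plan would print a relative risk and an interval for a sparse outcome that depend on the choice of numerator. For (b) with equal arms, the printed value is about 1.28 at an assumed 4 v 4 events, within a range of 1.66 (2 v 2) to 1.05 (20 v 20). This rests on 410 per arm, a vague prior, the natural reading of the summary wording, and the high-density interval being formed on the relative-risk scale. If (b) turns out not to be rare, the effect is a few per cent or less. No conclusion about efficacy or safety changes.

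**What to change.** For relative risks, report the posterior median with the equal-tailed 95% credible interval. Do this at least for exploratory outcome (b), and preferably throughout, so that relative risks follow the convention already used for hazard ratios. Amend the interval rule in Statistical principals to allow it. Keep the posterior mean for the absolute risk difference.

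Name this one summary and not a log-scale mean and interval as an alternative. The two differ when counts differ: at 10 v 3 events (Jeffreys prior, 410 per arm) the median is about 3.2 against 3.32 for the exponentiated mean log ratio. The equal-tailed interval is 1.02 to 13.3, against 0.96 to 12.3 for a high-density interval on the log scale, so they fall on opposite sides of 1.

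The cost is a change of wording. The same posterior draws serve, no model or decision rule changes, and it can be settled before the database lock, which the Trial status section expects by the end of September 2025.

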### Subgroup analyses

We will perform six planned subgroup analyses to estimate the subgroup-specific treatment effect for the primary outcome. These subgroups are:Patients aged < 6 months and ≥ 6 months.Patients who developed the first respiratory symptoms, including coryza and cough or fever, within 48 h of enrolment,Patients with a personal history of eczema,Patients with parents and/or siblings who have a history of atopy,Patients stratified by northern and southern hemispheres, andPatients stratified by receipt of nebulised or MDI-s medications: yes/no

For these subgroup analyses, we will perform relative risk regression with main effects for subgroup assignment and treatment group and an interaction between treatment and subgroup. Positive or negative subgroup effects will be declared if the interaction effect has a 99% probability of being greater or less than 0, respectively. We expect the treatment will be more effective in those participants with onset of illness within 48 h, a personal history of eczema, and a family history of atopy. We do not anticipate differences due to hemisphere of participating hospital or method of inhalation.

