## Method/Design

### Design and setting

The BIPED study is a phase III study conducted in 12 sites across Canada, Australia and New Zealand. All participating hospitals are members of the Pediatric Emergency Research Canada (PERC) network [11] or the Paediatric Research in Emergency Departments International Collaboration (PREDICT) [12], both of which are affiliated with the Pediatric Emergency Research Networks (PERN). The BIPED study will define bronchiolitis as an episode of wheezing or crackles in an infant aged between 60 days and 12 months, alongside signs of an upper respiratory tract infection during the period deemed to be the season for RSV bronchiolitis. To reflect international clinical guidelines and practice, we have not restricted our definition of bronchiolitis to the first episode of wheezing or crackles and will enrol infants with second and subsequent episodes of bronchiolitis, with each infant only enrolled once into the study.

The active treatment in the BIPED study is two treatments of epinephrine (either via nebulisation (3 mg) or via metered dose inhaler and spacer (MDI-s) (625 mcg)) given 30 min apart in the ED and two doses of once daily oral dexamethasone (0.6 mg/kg per dose, up to a maximum of 10 mg), known as EpiDex. The first dose of dexamethasone will be given immediately before the first dose of epinephrine, and the second dose will be given 24 h later. The BIPED study will compare EpiDex to a placebo control (oral dexamethasone vehicle and nebulised normal saline or an inert placebo by MDI-s) by randomising participants in a 1:1 ratio. All study personnel, bedside clinicians, and participants/caregivers are blinded to the study group assignment. Participants will be followed up for 21 days following their ED enrolment visit, with the primary outcome collected at 7 days (168 h) post enrolment.

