### Randomisation and data collection

Eligible participants will be randomised using permuted-block randomisation, stratified by site. This randomisation strategy ensures that differences in standard practice across sites will be equally represented in each study group. Additionally, block randomisation ensures that seasonal variation in the response to therapy will be comparable across the two groups. The statistician performing providing the randomisation lists is not involved in the study in another capacity.

Study participant research data will be stored using the REDCap electronic data capture system [14], based at a secure data coordination centre (DCC) at the Women and Children’s Health Research Institute (WCHRI), University of Alberta [15]. Individual participants will be identified with a unique study identification number.

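### The subgroup model's listed terms omit site, which is the randomisation stratum and is in the primary model; the cost is a small, conservative loss of precision

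*SAP article*

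**What the plan says.** Design. The trial is "conducted in 12 sites across Canada, Australia and New Zealand", allocating "by randomising participants in a 1:1 ratio". Under Randomisation and data collection: "Eligible participants will be randomised using permuted-block randomisation, stratified by site". The reason given there is that "differences in standard practice across sites will be equally represented in each study group".

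Primary model. Under Analysis for the primary endpoint, superiority is assessed "using hierarchical Bayesian relative risk regression, adjusted for site".

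Subgroup model. Under Subgroup analyses, six analyses of the primary outcome use relative risk regression with "main effects for subgroup assignment and treatment group and an interaction between treatment and subgroup". Neither site nor a hierarchical structure is mentioned. A subgroup effect is declared when the posterior probability that the interaction lies on one side of zero reaches 99%.

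Other models.
- Secondary: "Secondary outcomes one, two and three will be analysed using relative risk regression, like the primary outcome", so site can be read in.
- Safety: relative risk regression, with no mention of site and no link to the primary model.
- Exploratory: outcomes (a) to (d) "will be analysed using relative risk regression and report the posterior mean absolute-risk difference", without site. Site is named for (e) and (f), not for (g) or (h). Outcomes (i) and (j) are deferred.

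**The concern.** The article's own reason for stratifying is that practice differs between sites. The primary outcome is admission to hospital, which plausibly depends on local practice, so site is likely to be prognostic. When a trial balances on a prognostic factor and the analysis then ignores it, the stated uncertainty is larger than it need be. Interaction estimates are the least precise in the trial, so they can least afford this.

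There is also a question of consistency. The subgroup analyses qualify the primary result, and a reader will set the two side by side. An analyst who follows the subgroup section literally drops site, while one who assumes it carries over from the primary section keeps it. A pre-specified plan with a 99% declaration threshold should not leave both open.

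**Working it through.** **1. The text.** The plan shows inheritance from the primary model in one place, the link to the primary outcome used for secondary outcomes one to three. The subgroup section has no such link. Its list also includes the treatment main effect, which the primary model already contains, so it reads more like a full list of terms than a list of additions. No sentence extends site adjustment to every model; the only statement about all models, in the primary endpoint section, concerns priors.

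**2. The plan's figure.** No stated figure rests on this point. The sample size used below does reproduce: 410 / (1 − 0.05) = 431.6, so 432 per arm and 2 × 432 = 864 in total. The analysable number is 2 × 410 = 820.

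**3. Simulation inputs.**
- From the article: 820 infants, 12 sites, 1:1 within site, control risk about 0.35, target difference 0.08, hence a risk ratio of 0.27 / 0.35 = 0.77.
- Assumed: site shares from 20% down to 2%, normal site effects on the logit scale with SD 0 to 1.0, and no true interaction.
- Three subgroup types: patient-level (40% of infants, unrelated to site); fixed by site, as hemisphere is (5 of 12 sites); and correlated with site (85% against 15% prevalence).

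**4. Method.** Each of 600 data sets per setting was fitted twice with a log-link (modified Poisson) model: once with the listed terms only, and once with site indicators added. A normal approximation stands in for a flat-prior posterior. The ratio is the mean interaction SE without site divided by that with site.

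| Between-site SD | Patient-level | Fixed by site | Correlated with site |
|---|---|---|---|
| 0 | 0.2177 / 0.2177 = 1.000 | 0.2148 / 0.2136 = 1.006 | 0.2136 / 0.2129 = 1.003 |
| 0.3 | 0.2159 / 0.2143 = 1.007 | 0.2144 / 0.2118 = 1.013 | 0.2129 / 0.2108 = 1.010 |
| 0.6 | 0.2141 / 0.2084 = 1.028 | 0.2123 / 0.2062 = 1.030 | 0.2118 / 0.2062 = 1.027 |
| 1.0 | 0.2111 / 0.1981 = 1.065 | 0.2108 / 0.1983 = 1.063 | 0.2092 / 0.1964 = 1.065 |

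**5. A second scale.** A linear probability model (50/50 patient-level subgroup, 31% average risk) gives 0.0647 / 0.0646 = 1.002, 0.0650 / 0.0640 = 1.016 and 0.0654 / 0.0624 = 1.048 at SDs of 0.3, 0.5 and 0.8. Direction and size agree.

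**6. Bias.** The mean interaction estimate, with a true value of 0, was never further than 0.013 from zero on the log scale. The Monte Carlo error in that setting is 0.1990 / √600 = 0.008, so this is noise.

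**7. False declarations.** The nominal rate is 2% (1% in each direction). The observed rate was 1.5 to 2.5% without site and 1.7 to 2.7% with site. The Monte Carlo standard error is √(0.02 × 0.98 / 600) = 0.6 percentage points, so neither range departs from nominal.

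**The case against.** The strongest reply is that this is condensation. The primary section defines the plan's relative risk regression as hierarchical and adjusted for site, and later sections reuse the term. Secondary outcomes one to three take site by reference without naming it. Repeating site for exploratory (e) and (f) is natural, because the model there changes to Cox regression. The subgroup list does not claim to be exhaustive, and it omits priors that nobody supposes are dropped. This carries real weight: the intention may well be to keep site. It does not settle the matter, because the subgroup section writes out terms and lacks the link used for the secondary outcomes. Exploratory (h) also changes model class without naming site, and (g) names only patients as its level.

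A second reply is that the simulation is not the planned model. That is fair. It is frequentist and uses site indicators in place of a hierarchical site effect. It serves to size the effect, not to predict the trial's posterior.

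Three stronger readings are tempting, and the document does not support them:
- *Safety and most exploratory models exclude site.* Six of the eight exploratory outcomes analysed now, and the safety models, do not name it, but silence is not exclusion. Safety events may also be too few to support 12 site effects, so an unadjusted safety model can be defended if stated.
- *The omission makes subgroup claims unreliable.* Steps 6 and 7 show neither bias nor excess false declarations.
- *The hemisphere or device main effect absorbs site practice and distorts those subgroups.* Declarations rest on the interaction, and treatment is balanced within site. The article does not say that device is fixed by site.

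**Conclusion.** The point holds for the subgroup model and is minor. As written, the model leaves out the randomisation stratum and differs from the primary model for the same outcome. The consequence is conservative: interaction intervals about 1% wider at a between-site SD of 0.3, 2 to 3% at 0.6 and 6 to 7% at 1.0. These figures rest on assumed site sizes and site spread, neither of which the article reports, and on a normal approximation to the posterior. The upper end needs large differences between sites. For the safety and exploratory models the finding goes no further than that the plan should say whether site is included.

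**What to change.** Under Subgroup analyses, state that the model is the primary hierarchical relative risk regression with its site random effect retained, plus the subgroup main effect and the treatment-by-subgroup interaction. A random site effect matters for the hemisphere subgroup: hemisphere is fixed by site, so fixed site effects would absorb its main effect, whereas a random effect keeps it estimable.

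For each safety and exploratory model, add a few words saying whether site is included, and give the reason (such as sparse events) where it is not.

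The cost is wording and slightly longer computation. Site is already needed for the primary model. The change should be made before the database lock, which the article anticipates by the end of September 2025.
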